### **8.2.3 Eliciting Adverse Event Information**

All participants will be asked about any health related problems at each visit. Biochemical testing will occur as per the protocol. Adverse events will be recorded in case report forms.

## **8.3 Handling of Withdrawals**

A participant may be withdrawn from the study if he/she becomes ineligible based on inclusion/exclusion criteria e.g. becomes pregnant, develops an acute psychiatric problem.

Participants may withdraw from the study at any time. Those who withdraw will be encouraged to schedule a follow-up visit with their GP or physician.

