### **7.2.4 Fitbit®**

Participants who reach week 16 will be given a Fitbit® Flex 2 wristband to increase motivation and adherence to the intervention. Fitbit® activity monitors measure physical activity and sleep patterns. Various physical activities including running, outdoor bike riding, football, basketball, swimming and aerobic workouts can be tracked by the monitor, as well as simple steps. This is achieved using a 3 axis accelerometer which identifies the intensity of the activity being performed. The Fitbit® can also track sleep duration if worn to bed. Fitbit® devices have been shown to adequately measure both sleep and activity when compared to gold standard methods, however the accuracy and reliability of these measures is under examination [35, 36].

Participants' physical activity and sleep data will be accessed and downloaded by the study team. Data collection will only take place during week 16 and week 52, when participants are actively involved in the study. Participants who have been given a Fitbit® but withdraw from the study, will not have their data accessed after their withdrawal date. Participants will be encouraged to wear the Fitbit® during week 16 and week 52. Participants' data will be used for studies related to physical activity and sleep patterns. Fast Track dietitians will also access participants' Fitbit® accounts during diet reviews. For example, physical activity information may be used when discussing exercise or evaluating physical activity goals. Similarly, sleep data may be used by the dietitian when discussing sleep hygiene. Participants will be asked to create a Fitbit® account online or via the Fitbit® application. The study team and dietitian will log on to this account to access information recorded by the Fitbit®. This information is owned by the participant, therefore consent must be obtained before accessing and downloading the data.

A Fitbit® information sheet and consent form will be provided at week 16 to participants and their parent/guardian. A copy of the signed consent form will be given to participants and the hardcopy will be stored by the study team. It is not essential for this data to be collected, participants do not have to allow the study team to access their information, nor do they have to create an account to use the

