## 7.7 Inclusion Criteria

- Adolescents aged 13–17 years (inclusive)
- Obesity (defined as equivalent to adult BMI 30–45 kg/m^2) [58] and at least one of the following metabolic complications:
  - o Pre diabetes: impaired fasting glucose 5.6-6.9mmol/L and/or impaired glucose tolerance 2 hour post load 7.8-11.1mmol/L
  - o Insulin resistance: fasting insulin (pmol/L)/glucose(mmol/L) ratio >20
  - o Presence of acanthosis nigricans
  - o Hypertension: systolic and/or diastolic blood pressure above the 90th percentile for sex, age and height
  - o Low HDL-C <1.03mmol/L
  - o High triglycerides ≥ 1.7mmol/L
  - o Abnormal Alanine Transaminase (ALT) or Gamma-Glutamyltransferase (GGT) based on standard PowerChart cut-points (i.e. ALT or GGT >45 U/L)
  - o Diagnosis of polycystic ovary syndrome (PCOS)

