## 7.8 Exclusion Criteria

- Secondary obesity
- Significant intellectual disability as documented by the referring doctor
- Significant medical or psychiatric illness
- Previous diagnosis of Type 2 Diabetes Mellitus
- Currently undergoing treatment for a clinical eating disorder

- Pregnancy, or planning to become pregnant within the next 18 months
- Taking medications that have an effect on weight in the short term (excluding metformin)
- Adolescent or parent with poor level of spoken English
- Current enrolment in a weight loss program
- BMI in excess of 45kg/m^2

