### 8.2 Adverse Event Reporting

#### 8.2.1 Definitions

An adverse event is any undesirable sign, symptom or medical condition occurring after starting the study therapy (the IER diet). A medical condition/disease present before starting the study treatment will only be considered an adverse event if it worsens after starting the study treatment.

Pregnancy will be reported as an adverse event and followed to determine the outcome. Any study participant who becomes pregnant during the study will be withdrawn from the study.

A serious adverse event is an undesirable sign, symptom or medical condition which,

- (1) is fatal or life-threatening,
- (2) requires admission to hospital as an inpatient,
- (3) results in persistent or significant disability/incapacity,
- (4) constitutes a congenital anomaly or birth defect,
- (5) is medically significant, may jeopardize the participant and may require medical or surgical intervention to prevent one of the outcomes listed above.

A SUSAR is a serious adverse event that is suspected to be related to the study but unexpected.

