## **9.3 Statistical Methods to Be Undertaken**

Data analyses will be carried out according to a pre-established plan, with the primary analysis based on intention to treat and with statistical support from the Biostatistician in the Office of Research, CHW. Analysis will be undertaken blinded. The difference in BMI z-score between groups at 52 weeks will be assessed using a t-test. Mixed models will also be used to investigate changes over time. The mixed models procedure will take into account within participant correlations and missing data points. A time by group interaction will be included to investigate whether rates of change of weight loss were significantly different between the two study groups. A/[name] along with SCHN statistician [name] will oversee the statistical analyses.

Post hoc analysis will compare protocol adherers to non-adherers. An adherer will be defined as an individual who attends at least half of their scheduled appointments across the 12 month study period (either face to face or electronic). Additionally, at 52 weeks in measurement of the primary outcome (BMI z-score), a variation of plus or minus 4 weeks (i.e. measurement between 48 and 56 weeks) will be considered within protocol.

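### Withdrawal for ineligibility or pregnancy is from the study itself, with no outcome visit named afterwards, so data on possible harm and the 52-week endpoint can be lost

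*Protocol*

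**What the plan says.** The rule in section 8.3 reads: "A participant may be withdrawn from the study if he/she becomes ineligible based on inclusion/exclusion criteria". Its two examples are pregnancy and an acute psychiatric problem. The wording is permissive, and what the participant leaves is the study, not only the diet. For aftercare the section adds: "Those who withdraw will be encouraged to schedule a follow-up visit with their GP or physician". It mentions no week 16 or week 52 assessment for these participants.

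Section 8.2.1 (Definitions) is mandatory on one of the same examples: "Any study participant who becomes pregnant during the study will be withdrawn from the study".

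The only explicit statement on data after withdrawal is in section 7.2.4 and concerns activity-monitor data alone. Participants who were given a device but "withdraw from the study, will not have their data accessed after their withdrawal date".

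Section 9.3 sets out a t-test of BMI z-score at 52 weeks, "with the primary analysis based on intention to treat", and mixed models that are said to allow for missing data points. Section 8.4 states that withdrawals are not replaced, that the sample size allows for 30% attrition, and that withdrawals are assumed equal between the arms.

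**The concern.** Entry criteria are being used after randomisation as grounds for leaving the study. That matters most where the ground for leaving is itself something the trial needs to observe. Section 5.2 names disordered eating as a possible safety concern of intermittent energy restriction, and section 5.3 returns to it. Section 6.3.2 lists psycho-behavioural outcomes at weeks 16 and 52, and section 8.2.2 has an oversight committee review the psychological questionnaire data. Under section 8.3, a participant with an acute psychiatric problem can leave exactly those data.

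The primary comparison is also affected. A t-test at 52 weeks uses the participants who were measured. If removal depends on how a participant is doing, and differs between the arms, the measured groups are no longer the randomised groups. Section 8.3 does not say who decides or whether that person is unaware of the arm. Section 7.4 blinds the outcome assessors only.

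An analysis plan cannot settle this afterwards, because it cannot supply measurements that were never taken.

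**Working it through.** **Step 1: the passages side by side.**
- Ineligibility arising after entry: withdrawal *may* follow (8.3).
- Pregnancy: withdrawal *may* follow (8.3, as an example), and *will* follow (8.2.1). The two must be reconciled.
- Stopping the diet while remaining under observation: not described in either section.
- Outcome visit after withdrawal: none named, only a GP or physician visit (8.3).
- Analysis: intention to treat, t-test at 52 weeks, mixed models in addition (9.3). No sentence excludes withdrawn participants from analysis.

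**Step 2: reproduce the plan's sample size (sections 9.1 and 9.2).** Inputs: difference 0.12, SD 0.24, two-sided 0.05, power 80%.

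n per arm = 2 × (1.960 + 0.842)² × (0.24 / 0.12)² = 2 × 7.85 × 4 = 62.8, so 63. Solving with the t distribution gives 63.8, so 64. The plan states 65, which is within two participants. Inflation: 130 / 0.70 = 185.7, so 186, as stated.

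**Step 3: possible bias.** The protocol gives no rate for these withdrawals, so the following is illustration. Let a share w of one arm be withdrawn, with mean 52-week BMI z-score k SD away from that of the participants retained in that arm. The full-arm mean is (1 − w) × retained mean + w × withdrawn mean. The retained mean therefore misses the full-arm mean by w × k × 0.24. With no such loss in the other arm, this is the bias in the difference. The percentage is of the 0.12 target.

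| w | k = 0.5 | k = 1 | k = 2 |
|---|---|---|---|
| 2% | 0.0024 (2%) | 0.0048 (4%) | 0.0096 (8%) |
| 5% | 0.0060 (5%) | 0.0120 (10%) | 0.0240 (20%) |
| 10% | 0.0120 (10%) | 0.0240 (20%) | 0.0480 (40%) |

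If both arms lost the same share with the same k, the two errors would cancel. Equal numbers of withdrawals, as section 8.4 assumes, are not enough: the withdrawn participants must also differ from the retained ones to the same degree.

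**Step 4: power.** Power = Φ(0.12 / (0.24 × √(2/n)) − 1.96), with n = 186 × (1 − 0.30 − extra loss) / 2 per arm.
- No extra loss: n = 65.1, power 81%.
- 2% extra: n = 63.2, power 80%.
- 5% extra: n = 60.5, power 78%.
- 10% extra: n = 55.8, power 75%.

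If these withdrawals are already part of the 30%, the first line applies and nothing changes.

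**The case against.** The strongest reply is that section 8.3 is a permissive clause with two rare examples, and that the safety information is not simply lost. Adverse events are followed until resolution or stabilisation, even beyond the end-of-study visit (7.2.6, 8.2.2). Pregnancies are followed to outcome (8.2.1). Participants flagged as at risk are assessed by a psychologist (7.2.2, 7.5). Withdrawals by investigators for safety reasons related to the intervention count towards a stopping rule at more than 5% of participants (8.2.2). All of this stands. It secures event reports and clinical care. It does not secure the week 16 and 52 questionnaires or the BMI z-score, which are what the randomised comparison uses.

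A second reply is that missing-data methods belong in an analysis plan, which is not available here, and that the mixed models can use visits before withdrawal. This is fair as far as it goes. Those models are valid if the data are missing at random given what was observed. That is doubtful when the reason for leaving is a new psychiatric problem that the earlier visits may not foreshadow.

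A reader might also infer several stronger claims that the documents do not support:
- *That participants who succeed are removed because their BMI falls below the entry range or a metabolic complication resolves.* The calculated goal weight corresponds to an adult BMI of 25, below the entry threshold of 30, and those who reach it stay in the study with a maintenance option (7.2.2). Removal for success is plainly not intended.
- *That turning 18 triggers withdrawal.* The trial admits 17-year-olds to 52 weeks of intervention and offers a visit at 24 months (7.7, 7.2.2).
- *That the rule contradicts intention to treat.* Nothing excludes withdrawn participants from analysis or moves them between arms.
- *That every such case adds to the attrition allowance.* Section 8.4 sets withdrawals beside the 30%, so they plausibly fall inside it.

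For pregnancy the case is also weaker. A BMI z-score measured during pregnancy is hard to read as an effect of diet, so a missing value there is less clearly a defect.

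**Conclusion.** The point holds as a gap in trial conduct. Sections 8.2.1 and 8.3 treat leaving the diet and leaving the study as one act, name no outcome visit afterwards, and disagree on whether withdrawal for pregnancy is required or optional. The acute psychiatric case is the clearest, because it is the protocol's own example and bears on a safety question that the trial sets itself.

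The size is probably modest. The central illustration is a bias of 0.012, or 10% of the target difference, with a range of 2% to 40%. It rests on assumed one-sided withdrawal of 2–10% and an assumed gap of 0.5–2 SD. The bias is small unless such withdrawals are frequent, unequal between the arms and strongly related to outcome. No change in sample size follows. The case for acting is that the remedy is cheap and cannot be applied after the data have been missed.

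**What to change.** Amend sections 8.2.1 and 8.3 to:
1. State that the inclusion and exclusion criteria determine eligibility at enrolment.
2. Separate stopping the allocated diet, a clinical decision left to the clinicians, from leaving follow-up.
3. State that participants who stop the diet are still invited to the scheduled week 16 and week 52 assessments, where consent continues and it is clinically appropriate, and are analysed as randomised.
4. Reconcile the mandatory wording on pregnancy in 8.2.1 with the permissive wording in 8.3. Which rule applies is for the clinical team to settle.
5. State how weights measured during pregnancy are handled in the analysis.

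The cost is a short amendment and a small number of extra attendances at visits already in the schedule.

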## **8.4 Replacements**

If participants withdraw they will not be replaced. Our sample size estimation accounts for a 30% attrition rate and we assume withdrawals will be equal between groups.

# **9 Statistical Methods**

## **9.1 Sample Size Estimation & Justification**

Our primary outcome is the difference in BMI z-scores between dietary intervention groups at 52 weeks. Based on our power calculations (see below) and assuming 30% attrition rate (which is consistent with attrition rates at 52 weeks of 23% for our RESIST study [16] and 30% for our Loozit study [7] we will recruit 186 adolescents; 124 at The Children's Hospital at Westmead; 62 at Monash) over an 18 month period.

Recruitment strategies are outlined above (please see 8.1.1 Recruitment).

### ***The Children's Hospital Westmead***

We will recruit 124 patients in total at The Children's Hospital at Westmead. We anticipate that we will recruit 40 from current hospital referrals and the remainder from the community. The Adolescent Weight Management Service provides a dietetic and medical clinic twice per month. The service currently receives 6-8 referrals per months on average, and has a waiting list of 12 months. Overall 6.1% of Australian adolescents are obese [1] which is higher in Western Sydney[59, 60]. Assuming the adolescent population in Western Sydney is ~270,000 [60] there will be at least 16,500 adolescents with obesity. We will need to recruit 0.5% of this population from the community.

### ***Monash University and Monash Children's Hospital***

We will recruit 62 patients in total at Monash. We anticipate we will recruit 50% from the existing Obesity Management Clinic at Monash Health under the direction of [name] and the others from generating new referrals from the community including local GPs and practice nurses. Pediatricians who consult at the newly opened Monash Children's Hospital will also be contacted in order to refer patients to the study who they see, but who they may not usually refer to an obesity service which is currently designed for complex conditions and those with co-morbidities.

## **9.2 Power Calculations**

The Therapeutic Goods Administration (TGA) defines successful weight loss as at least a 5% decrease in initial bodyweight in adults. This is approximately equivalent to a 0.12 decrease in BMI z-score in adolescents. This intervention will be considered successful if there is a 5% difference between groups at 52 weeks as defined by the TGA [61].

Assuming a BMI z-score difference at 52 weeks of 0.12 and a SD 0.24 (based on our previous RCT of age and weight matched participants [61]; 80% power, and a two-sided significance level of 0.05, a sample size of 65 adolescents per group, 130 in total, is required. As indicated above we anticipate a 30% attrition rate and we will recruit 186 adolescents.

## **9.3 Statistical Methods to Be Undertaken**

Data analyses will be carried out according to a pre-established plan, with the primary analysis based on intention to treat and with statistical support from the Biostatistician in the Office of Research, CHW. Analysis will be undertaken blinded. The difference in BMI z-score between groups at 52 weeks will be assessed using a t-test. Mixed models will also be used to investigate changes over time. The mixed models procedure will take into account within participant correlations and missing data points. A time by group interaction will be included to investigate whether rates of change of weight loss were significantly different between the two study groups. A/[name] along with SCHN statistician [name] will oversee the statistical analyses.

Post hoc analysis will compare protocol adherers to non-adherers. An adherer will be defined as an individual who attends at least half of their scheduled appointments across the 12 month study period (either face to face or electronic). Additionally, at 52 weeks in measurement of the primary outcome (BMI z-score), a variation of plus or minus 4 weeks (i.e. measurement between 48 and 56 weeks) will be considered within protocol.

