### **Results from previous weight management studies in adolescents**

Our group has undertaken the largest number of clinical trials of adolescent obesity management in Australasia, in both hospital and community settings. Our studies have shown that:

- Decreases in BMI and BMI z-score are associated with improvements in measures of self-esteem, health-related quality of life and a range of cardiometabolic risk factors[6, 7]. These persist for 2 years from baseline and >18 months from the end of intensive weight-management treatment.
- Adolescents seeking treatment for obesity have a strong preference for structured eating plans rather than unstructured advice [8].
- Adolescents given a prescriptive diet (under the supervision of health professionals) show improvements in eating behaviours at 6 months, including a reduction in emotional eating and eating in response to external cues, and experience no adverse effect on dietary restraint [9].
- Weight loss at 3 months from baseline is a strong predictor of adherence to, and participation in, the treatment program and better weight outcomes at 2 years [10].
- Additional mHealth support strategies (such as phone coaching, SMS messages or emails) are very acceptable to young people involved in weight loss trials [11, 12].
- Adolescents with obesity and newly diagnosed type 2 diabetes who are given a closely supervised very low energy diet (VLED) have significant weight loss of 3.9% (range, 0.6-7.8%) at 4 weeks and 5.0% (range, 2.8% gain to 8.8% loss) at 8 weeks, with marked improvements in diabetes control [13]. However, the diet is severe and may not suit all as a longer term form of therapy.
- Adherence to a calorie restricted diet, rather than the type of diet prescribed, is key to successful weight loss and improved metabolic factors at 12 and 24 months, regardless of macronutrient content [10, 14-16].

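### The primary analysis is called intention to treat, but the only test named for week 52 uses only participants measured then, and the mixed model that handles missing data comes second

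*Protocol*

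**What the plan says.** Section 9.1 makes the week-52 between-group difference in BMI z-score the primary outcome. Section 9.3 sets out the analysis "with the primary analysis based on intention to treat" and assigns a t-test to that difference. Mixed models are then added to study change over time, with a time-by-group interaction aimed at rates of change. Missing data are mentioned only there: "The mixed models procedure will take into account within participant correlations and missing data points". Nothing is said about how a missing week-52 value would enter the t-test.

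On attrition, section 9.2 states: "we anticipate a 30% attrition rate and we will recruit 186 adolescents". Section 9.1 supports this with 52-week attrition of 23% and 30% in two earlier trials by the group. Section 8.3 directs those who withdraw to their own GP or physician and mentions no week-52 study measurement for them. Section 8.4 adds: "we assume withdrawals will be equal between groups".

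On the link between weight and staying in, section 5.3 (results from previous studies) reports: "Weight loss at 3 months from baseline is a strong predictor of adherence to, and participation in, the treatment program". Elsewhere section 5.3 proposes better long-term adherence on IER, and section 7.2.2 (active control arm) expects greater weight loss on IER.

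**The concern.** Intention to treat means that everyone randomised counts in the arm to which they were allocated. A t-test on week-52 values cannot include a person who has none. As written, the label and the method do not fit together under the attrition that the protocol itself plans for.

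What is at stake is the trial's only primary result. Early weight change may influence who stays. If the arms also differ in early weight change, or the influence is stronger in one arm, those measured at week 52 are no longer comparable between arms. The margin is narrow: section 9.2 equates the success criterion with roughly 0.12 BMI z-score units, so an error of a few hundredths could change the reading of the trial.

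**Working it through.** **1. The sample size reproduces.** Inputs from section 9.2: "Assuming a BMI z-score difference at 52 weeks of 0.12 and a SD 0.24", 80% power and "a two-sided significance level of 0.05".

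- Normal approximation: n per arm = 2 × (1.96 + 0.84)² × (0.24/0.12)² = 2 × 7.85 × 4 = 62.8, so 63.
- Exact t-test at standardised difference 0.5: 63.8, so 64 per arm.
- The protocol states: "a sample size of 65 adolescents per group, 130 in total, is required". Power at 65 per arm is 80.8%.
- Inflation: 130 / 0.70 = 185.7, so 186.

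The figures are sound. They also show that the t-test is sized on the 70% expected to have a week-52 value.

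**2. How many the t-test would leave out.**

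- At 30% attrition: 186 × 0.30 = 55.8, about 56.
- At 23% attrition: 186 × 0.23 = 42.8, about 43.

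**3. Whether dropout could differ by arm.** Three months falls in Phase 2 (weeks 5 to 16, section 7.2.2), when the arms are already on different diets. If early weight loss helps retention and IER produces more of it, as the trial hopes, retention would differ by arm.

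**4. What that could do to the t-test.** A large-sample simulation used the protocol's difference of 0.12 and SD of 0.24. The following are assumptions, not protocol figures: an early BMI z-score change, also with SD 0.24, correlated 0.5 to 0.7 with the week-52 value; 30% dropout overall; and dropout odds 2 to 5 times higher per SD of worse early change. The comparison method regressed the week-52 value on early change within each arm and averaged over everyone randomised. It stands in for a mixed model under missing at random.

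| Case | Dropout, control / IER | t-test | Model using early weight |
|---|---|---|---|
| (a) Same mechanism in both arms, no early arm difference | 30% / 30% | 0.120 | about 0.12 |
| (b) Same mechanism, early arm difference 0.06 to 0.12 | 32% / 28% to 36% / 24% | 0.117 to 0.100 | about 0.12 |
| (c) Mechanism in the IER arm only | 30% / 30% | 0.142 to 0.178 | about 0.12 |

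**5. Scale.** The standard error of the planned t-test is 0.24 × √(2/65) = 0.042.

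- Case (b): bias of 0.003 to 0.020 towards no difference, at most about half a standard error. Power at 65 per arm falls to between about 80% and 71%.
- Case (c): bias of 0.022 to 0.058 in favour of IER, up to about 1.4 standard errors, although both arms lose the same proportion.

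**The case against.** **The protocol never says complete-case.** Section 9.3 refers to a pre-established plan, which is not at hand and could impute before the t-test. This stands in part. A reader might infer that the protocol commits to dropping incomplete participants, and its text does not go that far. But the protocol does choose the method for the primary outcome, and nothing in it points to imputation.

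**Missing data are addressed in the same section.** The mixed model is planned, and with time as categories it would give the week-52 contrast. This stands, and it is why the remedy is cheap. But the protocol does not give that contrast the primary role.

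**The evidence on early weight loss is indirect.** It comes from the group's earlier work and concerns taking part in the programme, not a missing week-52 measurement. A reader might take it as a statement that dropout in this trial depends on weight loss. It supports only a reasonable inference.

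**Dropout related to weight need not bias the t-test.** Correct: case (a) shows none. Bias needs an early arm difference or a mechanism that differs by arm. Both arms share the same initial diet for up to 4 weeks and diverge only afterwards. Still, an early arm difference is what the trial's hypothesis leads one to expect.

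**Equal withdrawals accompany the sample-size statement.** Correct. The sentence in section 8.4 is not an analysis assumption, and expecting better adherence to a diet does not directly contradict it. It need not be deleted. It gives no protection either, as case (c) shows.

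**Conclusion.** The point holds as a mismatch between label and method. As written, the primary test uses only those measured at week 52, leaving out about 43 to 56 of 186 randomised on the protocol's planning figures, while the analysis suited to incomplete follow-up is secondary.

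The direction and size of any bias are not known. A reader might conclude that the test must understate the IER effect. Cases (b) and (c) point in opposite directions, and case (a) gives no bias. The ranges of about 0.10 to 0.117 and 0.14 to 0.18, against a true 0.12, rest on assumed correlations, early differences and dropout odds that the protocol does not supply. The model using earlier weights recovers 0.12 because those cases make dropout depend only on early weight that was observed. If dropout depends on unobserved later weight, that model can be biased too, so a sensitivity analysis is still needed.

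**What to change.** Reword section 9.3 before any unblinded analysis:

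- **Primary analysis:** the mixed model already planned, with all randomised participants as allocated; BMI z-score at baseline and the scheduled post-baseline visits up to week 52; time as categories; arm-by-time terms; and adjustment for baseline. The primary estimate is the arm difference at week 52 with its 95% confidence interval.
- **Sensitivity analyses:** the t-test on those measured at week 52, described as such, and a delta-shift analysis in which unobserved week-52 values are made progressively worse than the model predicts, separately by arm.
- **Section 8.4:** keep equal withdrawals as a planning assumption only, and do not rely on it for the validity of the comparison.

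If the t-test is to stay primary, section 9.3 should at least say how missing week-52 values enter it.

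The cost is rewording plus a little more analysis work. Weight and height are already scheduled at visits before week 52, and the sample size does not change.

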#### **6.3.1 Primary Outcome**

BMI z-score at 52 weeks.

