## 7.2 Study Type & Design & Schedule

### 7.2.1 Study Design

This is a prospective, randomised, multi-centre study designed to determine if IER results in lower BMI z-score after 52 weeks of intervention in adolescents with obesity, compared with a standard, usual care, hypocaloric dietary intervention. A total of 186 participants aged 13–17 years will be randomised on a 1:1 ratio to 4 weeks of VLED, followed by 48 weeks of IER (experimental arm), or 4 weeks of VLED, followed by 48 weeks of current best-practice calorie restricted diet (active control arm). To ensure even distribution, randomization will be stratified by clinical study site, age, sex and BMI. Randomisation will occur at baseline and participants will be informed of their allocated dietary patterns during phase 1.

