## 7.4 Randomisation

After completion of screening visits, participants will be randomly allocated to one of the two intervention groups, using a computer-generated randomisation schedule (1:1) from the NHMRC Clinical Trials Centre (University of Sydney). Random allocation will occur via a process of minimisation with allocations concealed, and stratified by intervention site, age (13–14 years; 15–17 years), sex and body mass index (BMI) (equivalent to 30–34.9 kg/m^2; 35–45 kg/m^2). Forced allocation will be used for participants who have a family member enrolled in the study to keep family members within the same study arm. The Interactive Voice Response System (IVRS) at the NHMRC Clinical Trials Centre is able to force the allocation of a new participant based on a previously randomised participant (based on the ID number). These new participants will be included in the stratification tables used to randomise subsequent participants. Assessors for the primary outcome (BMI z-score at 52 weeks) and secondary outcomes will be blinded to treatment allocation.

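### The primary test in 9.3 is an unadjusted t-test on 52-week BMI z-score; it is valid, but it discards baseline BMI z-score and the minimisation factors, and 9.2 does not say which SD 0.24 is

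*Protocol*

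**What the plan says.** Section 6.3.1 defines the primary outcome as a level, not a change: "BMI z-score at 52 weeks". Section 9.3 gives the test: "The difference in BMI z-score between groups at 52 weeks will be assessed using a t-test". No covariate is attached to it. The same section adds a supporting analysis, "Mixed models will also be used to investigate changes over time", with a group-by-time term, and again names neither baseline nor the allocation factors as covariates. It refers to a separate analysis plan, which is not at hand.

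Section 7.4 allocates by minimisation, "stratified by intervention site, age (13–14 years; 15–17 years), sex and body mass index (BMI" in two bands). Table 2 schedules weight and height at baseline, so baseline BMI z-score should be available for the randomised participants.

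Section 9.2 sizes the trial: "Assuming a BMI z-score difference at 52 weeks of 0.12 and a SD 0.24", citing an earlier trial by the group, and then "80% power, and a two-sided significance level of 0.05, a sample size of 65 adolescents per group, 130 in total, is required". After allowance for loss, "we anticipate a 30% attrition rate and we will recruit 186 adolescents". It does not say whether 0.24 is the SD of the 52-week value, of the change from baseline, or a residual SD after adjustment.

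**The concern.** The design balances the arms on BMI and then compares a later BMI measure as if no balancing had been done and no baseline were known. Two things follow.

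- **Efficiency.** Differences between participants that were already present at baseline stay in the error term. The interval for the diet effect is wider than the collected data require.
- **Conservatism.** Minimisation makes the arms more alike on the chosen factors than simple randomisation would. A standard error that ignores predictive factors is then too large on average. This lowers the false-positive rate below its nominal level; it does not raise it.

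The unlabelled SD adds a separate uncertainty. The target of 0.12 in 9.2 is derived from a within-person loss of 5% of body weight, whereas the test compares levels between people. If the SD of 0.24 also came from changes, the power statement would describe a different analysis from the one in 9.3.

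What is at stake is the precision of the primary result, and whether the stated power belongs to the stated test.

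**Working it through.** **Inputs from the protocol.** Difference 0.12, SD 0.24, two-sided 0.05, 80% power, 65 per arm, 30% attrition, 186 recruited (9.2); 1:1 allocation (7.2.1).

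**Input not in the protocol.** The correlation *r* between baseline and 52-week BMI z-score. It is assumed, and results are shown over a range.

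**Step 1: reproduce the plan's figure.** Normal approximation: n per arm = 2 × (1.96 + 0.8416)² × 0.24² / 0.12² = 2 × 7.849 × 4 = 62.8, so 63. The exact two-sample t-test needs 63.8, so 64. The stated 65 is within 2 of both, and power at 65 per arm is 80.8%. Attrition: 130 / 0.7 = 185.7, so 186; conversely 93 × 0.7 = 65.1 per arm. The calculation reproduces for an unadjusted comparison of two means, which is the test in 9.3.

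**Step 2: reading A, 0.24 is the SD of the 52-week value.** The residual SD after baseline adjustment is 0.24 × √(1 − r²), and the unadjusted interval is 1/√(1 − r²) times as wide as the adjusted one. Power is for 65 per arm; the few degrees of freedom spent on covariates are ignored.

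| r (assumed) | Residual SD | t-test power | Adjusted power | Interval ratio |
|---|---|---|---|---|
| 0.3 | 0.229 | 80.8% | 84% | 1.05 |
| 0.5 | 0.208 | 80.8% | 90% | 1.15 |
| 0.7 | 0.171 | 80.8% | 98% | 1.40 |
| 0.8 | 0.144 | 80.8% | 99.7% | 1.67 |

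**Step 3: reading B, 0.24 is the SD of change.** With equal variances at the two times, SD of change = SD₅₂ × √(2(1 − r)), so SD₅₂ = 0.24 / √(2(1 − r)). The residual SD is SD₅₂ × √(1 − r²).

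Example at r = 0.7: SD₅₂ = 0.24 / √0.6 = 0.310 and residual SD = 0.310 × √0.51 = 0.221.

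| r (assumed) | SD at 52 weeks | t-test power | Residual SD | Adjusted power |
|---|---|---|---|---|
| 0.5 | 0.240 | 81% | 0.208 | 90% |
| 0.7 | 0.310 | 59% | 0.221 | 87% |
| 0.8 | 0.379 | 43% | 0.228 | 85% |
| 0.9 | 0.537 | 24% | 0.234 | 83% |

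Under reading B the t-test falls short only when r exceeds 0.5. At r = 0.3 it would have 92%.

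**Step 4: compare.** The adjusted analysis exceeds 80% power in every row of both tables. The t-test reaches 80% throughout reading A, but under reading B only for r up to about 0.5.

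**The case against.** The strongest reply is that nothing in the plan is wrong. The trial was sized for this same unadjusted comparison and the arithmetic reproduces. Sections 6.3.1, 9.2 and 9.3 all speak of the value or difference at 52 weeks, which favours reading 0.24 as the 52-week SD. An unadjusted t-test after minimisation is valid and errs on the cautious side. Mixed models that use the repeated measurements are also planned, and covariate lists are often left to the analysis plan.

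Much of this stands. A reader might infer that, because covariates are omitted, the stated 80% power will not be delivered. The documents do not support that. Omission only forgoes power above 80%; a shortfall needs the separate premise that 0.24 is smaller than the 52-week SD, which the protocol neither states nor excludes.

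A reader might also try to prove that premise from the entry range of BMI 30–45. Using the 5%-to-0.12 conversion in 9.2, the range spans about 0.95 z. A triangular or uniform spread then gives a baseline SD of 0.22 to 0.27, which seems to leave a change SD of only √(0.24² − 0.224²), about 0.09. This fails twice. Eligibility limits are not a distribution. The subtraction also assumes that change is independent of baseline: with baseline SD 0.224, 52-week SD 0.24 and correlation 0.7 to 0.8, the change SD is 0.18 to 0.15, which is coherent.

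The size of the conservatism cannot be established either. It depends on how much 52-week variance the factors explain, which the protocol does not give, and on balance surviving 30% attrition.

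The last two points in the reply do not dispose of the matter. The mixed models are additional, are aimed at change over time, and are given no baseline or allocation covariates. And the protocol does not leave the test open for an analysis plan to choose: it fixes a t-test.

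**Conclusion.** The point holds as one of efficiency and clarity, not validity. The primary test leaves out the baseline value of its own outcome and all four minimisation factors.

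If 0.24 is the 52-week SD, the planned power is met at 80.8%, and the cost is the gain forgone: about 90% at r = 0.5 and 98% at r = 0.7, with unadjusted intervals 1.15 and 1.40 times as wide. If 0.24 is an SD of change, the planned test has about 59% power at r = 0.7 and 43% at r = 0.8, against about 87% and 85% with adjustment.

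These figures assume the stated difference of 0.12, 65 analysed per arm, the values of r shown and, for the second reading, equal variances at baseline and 52 weeks. The direction of the conservatism follows from the design; its size is not established. Since the adjusted analysis keeps the planned power under both readings across the range shown, the change is worth making whichever SD 0.24 proves to be.

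**What to change.** **Section 9.3.** Make the primary analysis a linear model of 52-week BMI z-score on arm, baseline BMI z-score, site, age group and sex, or the week-52 contrast from a mixed model carrying the same adjustment. Continuous baseline BMI z-score largely covers the BMI stratum used in minimisation. Keep the unadjusted t-test as a sensitivity analysis. Settle the covariates before allocation is revealed to the analysts, because choosing them afterwards would not be credible.

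**Section 9.2.** State whether 0.24 is the SD of the 52-week value, of the change from baseline, or a residual SD after adjustment. Restate power for the analysis actually used, giving the correlation assumed if one is needed.

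**Cost.** About one sentence in each section. No new data, visits or participants are needed.
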